## Expected duration of trial

The end of the trial will be defined as the database being locked following all participants having made their final follow-up visit, the data entered into the database and all queries resolved.

Participant recruitment is expected to take approximately 16 months (4 months safety run and 12 months RCT stage). Follow-up will continue until the last recruited participant completes their 12-month follow-up visit.

## Trial assessments

The assessments in online supplemental table 1 all form part of the routine management of renal transplant patients (desirable assessments only required if being collected as part of routine clinical care) with the exception of the research samples being collected at Guy’s Hospital only.

### Assessment of safety

Specification, timing and recording of safety parameters

The following safety parameters will be collected at every visit.

AEs and concomitant treatment profile.Vital signs to include:Blood pressure, heart rate, respiratory rate, temperature, oxygen saturation, weight (required at day 0, desirable for subsequent visits) and height (only required at day 0).Haematology to include:Haemoglobin, platelets, haematocrit, red blood cells, mean cell volume, white blood cell, lymphocyte, basophil, monocyte, neutrophil, eosinophils.Serum biochemistry to include:Glucose, gamma-glutamyl transferase, potassium, sodium, creatinine, eGFR, total bilirubin, bicarbonate, alkaline phosphatase, phosphorus, total protein, magnesium, AST (aspartate aminotransferase)/ALT (alanine aminotransferase), albumin, calciumUrinalysis to include:Protein, specific gravity, glucose, pH, ketones, leucocytes, nitrites, urine sediment.Urine microscopy and culture.Tacrolimus blood levels.

The Investigator will review all laboratory reports and will sign and date them on the day of review. If there are any findings outside the normal range, the investigator will confirm whether the result is clinically significant or not. Any laboratory report indicated as being clinically significant will be recorded on the AE section of the eCRF.

AEs will be recorded from consent up until the end of a participant’s 12-month follow-up period. All SAEs will be followed-up for a further 30 days after the last participant’s final 1-year follow-up visit date or until resolution.

All SAEs, serious adverse reactions and suspected unexpected serious adverse reactions (SUSARs) will be reported immediately (and certainly no later than 24 hours) by the Investigator to the King’s Health Partners-Clinical Trials Office (KHP-CTO) and chief investigator (CI) for review in accordance with the current pharmacovigilance policy. The KHP-CTO will report SUSARs to the relevant ethics committee and to the Medicines and Healthcare products Regulatory Agency (MHRA).

Reporting timelines are as follows:

SUSARs which are fatal or life-threatening must be reported not later than 7 days after the sponsor is first aware of the reaction. Any additional relevant information must be reported within a further 8 days.SUSARs that are not fatal or life-threatening must be reported within 15 days of the sponsor first becoming aware of the reaction.

The CI and KHP-CTO (on behalf of the co-sponsors) will submit a Development Safety Update Report relating to this trial IMP to the MHRA and Research Ethics Committee (REC) annually.

All serious and non-serious AEs will be recorded in the eCRF from the time of consent including those listed above not being reported to the Sponsor.

Mirococept is administered to the kidney ex vivo and is cytotopic, very little is expected to enter the systemic circulation. In the Phase I study, doses up to 100 mg given systemically were tolerated well. The conclusions of that Phase I study (Ref: ME0579 (APT070/1)) have been summarised in the Background and are described in more detail in both the IB and Investigational Medicinal Product Dossier.

In the present protocol, we do not expect more than about 20% of the maximum dose administered to the graft to reach the systemic circulation. At the doses proposed, this estimated exposure lies in the range of 12–36 mg of drug. Therefore, we do not consider drug-related AEs to be likely.

#### Premature termination of the trial

The trial may be prematurely discontinued by the Sponsor, CI or Regulatory Authority on the basis of new safety information or for other reasons given by the Data Monitoring and Ethics Committee/TSC regulatory authority or ethics committee concerned.

If the trial is prematurely discontinued, active participants will be informed and no further participant data will be collected. The Competent Authority (MHRA) and Research Ethics Committee will be informed within 15 days of the early termination of the trial.

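### The early-termination rule ends all participant data collection, with no exception for open SAEs or already-treated recipients, and conflicts with the protocol's own safety follow-up

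*Protocol article*

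**What the plan says.** The protocol article treats follow-up in three places.

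- *Premature termination of the trial* sets the grounds for stopping: "The trial may be prematurely discontinued by the Sponsor, CI or Regulatory Authority on the basis of new safety information or for other reasons". If that happens, "active participants will be informed and no further participant data will be collected". No class of data and no group of participants is exempted.
- *Assessment of safety* sets the safety windows: "AEs will be recorded from consent up until the end of a participant’s 12-month follow-up period", and "All SAEs will be followed-up for a further 30 days after the last participant’s final 1-year follow-up visit date or until resolution". Neither sentence is conditional on the trial running to plan.
- *Expected duration of trial* sets overall follow-up: "Follow-up will continue until the last recruited participant completes their 12-month follow-up visit". It defines the end of the trial as database lock after all final visits.

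Two further sections bear on the point. *Trial assessments* says that the scheduled assessments "all form part of the routine management of renal transplant patients", apart from the research samples taken at Guy's Hospital. *Withdrawal of participants* keeps the data gathered before an individual withdraws and offers a withdrawal visit.

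**The concern.** New safety information is the first ground for stopping that the article names. In that situation, what happens next to recipients of treated kidneys is the information most needed: whether open serious events resolve, and whether rejection, graft loss or death follows. As written, the rule ends collection of that information on the day the trial stops. A participant still in the first week would have no recorded DGF status.

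The primary objective is to identify the safest and most efficacious dose. A truncated safety record would weaken the safety half of that objective and make it harder to characterise the signal that caused the stop. Early stopping is not a remote possibility: the predecessor trial was terminated after its first cohort, and this trial has a go/no-go review after the safety run.

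**Working it through.** **Comparing the texts.** The article states no figure on this point, so the main check is whether the rules can be followed together after an early stop.

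1. A participant with an unresolved serious adverse event on the stopping date: *Assessment of safety* calls for follow-up to resolution or to 30 days after the last 1-year visit. *Premature termination* says nothing further is collected. Both cannot be done.
2. A participant at month 4 with no event: *Assessment of safety* calls for adverse-event recording to month 12. *Premature termination* ends it at month 4.
3. A fatal or life-threatening SUSAR that prompts the stop: *Assessment of safety* allows a further 8 days for reporting additional relevant information. Gathering new participant information for that report would breach the termination rule as worded.
4. No sentence says which rule governs.

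**Illustration of size.** Inputs from *Sample size* and *Expected duration of trial*: 144 / (1 − 0.10) = 160 participants in the four-arm trial, which reproduces the article's target; 12 months of accrual in the randomised stage; 12 months of follow-up each. Assumptions: uniform accrual and no drop-out.

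For a stop at month s of the randomised stage, with s ≤ 12:

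- randomised: n = 160 × s / 12
- mean follow-up reached: s / 2 months
- uncollected share of planned participant-months: 1 − (s/2)/12 = 1 − s/24

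| Stop (month s) | Randomised | Observed participant-months | Planned | Uncollected |
|---|---|---|---|---|
| 3 | 40 | 60 | 480 | 87.5% |
| 6 | 80 | 240 | 960 | 75% |
| 9 | 120 | 540 | 1,440 | 62.5% |
| 12 | 160 | 960 | 1,920 | 50% |

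At month 18, after recruitment has closed, the first 80 have completed 12 months and the other 80 have a mean of 9. Observed is 80 × 12 + 80 × 9 = 1,680 of 1,920, so 240 / 1,920 = 12.5% is uncollected.

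The percentages do not depend on the number randomised, so they also apply if fewer doses go forward, provided accrual still takes 12 months. If all three doses go forward, about 3/4 × 80 = 60 of those randomised by month 6 would have received active drug. About 160 / 52 ≈ 3 participants would be inside the 7-day primary window on any stopping date during accrual.

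**12-month endpoints.** A participant randomised at month 0 reaches 12 months only at month 12, so a stop during recruitment leaves essentially no randomised participant with 12-month GFR, rejection or graft survival. The safety run differs. It recruits over the 4 months before the randomised stage, so with no gap between stages its first participant reaches 12 months at randomised-stage month 12 − 4 = 8, and its last by month 12.

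**The case against.** The strongest reply is that the termination sentence is a special rule for an unusual event, and that the safety and duration sections describe a trial that runs to plan. A specific rule displacing a general one is ordinary drafting, and the texts meet only if the trial is stopped. This stands in part: the clash is conditional on an early stop, and the special-rule reading removes the formal contradiction. It does not remove the problem, because the rule that remains ends safety collection on treated recipients when a safety concern has arisen.

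Secondly, not every safety action need trigger this rule. *Data Monitoring Committee* provides for continuation, modification or termination, so a halt to recruitment with continued follow-up could be handled as a modification. Some stops for other reasons might also make further collection impracticable. Both points are fair, but the article does not tie a safety stop to the modification route, and its termination rule names safety as a ground.

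Thirdly, the full protocol is not shown and may qualify the sentence. That is possible, but the article states the rule flatly, so this is not a detail merely left out of a condensed text.

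Four stronger readings are tempting, and the document does not support them:

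- *That safety data are discarded.* The rule forgoes future collection. Nothing deletes data already held, and data gathered before an individual withdrawal are expressly kept.
- *That no participant at all would have 12-month endpoints after a stop during recruitment.* Safety-run participants could, from about month 8 of the randomised stage.
- *That exposure to the drug continues through the lost follow-up.* The article says the drug is retained in the donor organ but gives no duration. The case rests on later outcomes in treated recipients, not on persisting exposure.
- *That the duration section itself requires adverse-event recording.* It sets follow-up; only the safety section sets adverse-event recording.

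**Conclusion.** The point holds as a conflict that arises if the trial is stopped early. The termination rule is explicit and unqualified, and in that event it cannot be applied together with the adverse-event and serious-adverse-event follow-up or the overall follow-up stated elsewhere. The consequence is loss of all further safety and outcome data on treated participants.

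The illustrative size is 75% of planned participant-months for a stop at month 6 of the randomised stage and 50% at month 12, falling to 12.5% at month 18. These figures rest on assumed uniform accrual, no drop-out and a hypothetical stopping date. They give no probability of stopping and would be the same for any trial on this timetable. No planned sample size, estimate or analysis is affected if the trial runs to completion. It should be corrected because the correction is small and has to be in place before any stop occurs.

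**What to change.** Reconcile *Premature termination of the trial* with *Assessment of safety* and *Expected duration of trial*. State that on early termination randomisation stops, but the data collection already scheduled continues for every participant whose kidney received study drug or placebo, unless that participant withdraws consent. At a minimum this covers DGF status, adverse and serious adverse events, rejection, graft and patient survival, and creatinine to 12 months. Say that the same applies to safety-run participants, and carry the wording into both versions of the participant information. The change concerns data collection only and alters no dose or clinical-management rule.

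The cost is more than one sentence of text. Recruitment began on 3 December 2024, so this is an amendment that goes to the ethics committee and regulators as appropriate. If a stop occurred, data entry, eCRF support, monitoring and site staff time would have to continue for those already enrolled. No new assessments are needed: apart from the Guy's Hospital research samples, the scheduled ones are described as routine care.

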## Statistics

EMPIRIKAL-2 is an operationally seamless adaptive design to evaluate safety and superiority of Mirococept in reducing DGF in deceased donor kidney transplantation, as compared with placebo. The trial is randomised, double blind and placebo controlled to minimise bias.

### Sample size

Nine patients will be needed for the safety run. Allowing for a 10% drop-out rate, the target sample size will be 10 patients for this stage.

For the main multi-arm randomised placebo-controlled stage, the required sample size was calculated using a selection theory approach as proposed by Simon *et al*.^26^ Software from the Centre for Clinical Research and Biostatistics, Hong Kong was used: (https://www2.ccrb.cuhk.edu.hk/stat/phase2/Randomized.htm).

The parameters for this calculation are p=0.30, D=0.20 and k=4, where p is the estimated percentage of the lowest response rate among all treatments, D is the difference in response rate between the best dose of Mirococept and all the other treatment groups including placebo, and k is the number of treatment arms.

A sample size of 144 (36 in each arm) will be required to correctly identify the best dose of Mirococept with 90% probability. 30 patients per arm will be required if two of the proposed doses are well-tolerated and 20 patients per arm if only one dose is well-tolerated in the safety run. Allowing for a 10% drop-out rate, the target sample size for a 4-arm study will be 160 participants (40 in each arm).

Overall, up to 170 participants are needed for the safety component and main randomised study.

A sample size of 40 per arm will produce a two-sided 95% CI for the difference in population proportions with a precision that is equal to ±21.1% when the estimated DGF rate in the treatment arm is 30% (vs 50% in placebo).

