**Methods and analysis:**

EMPIRIKAL-2 is a Phase IIa multicentre double-blind randomised controlled trial (RCT) with an initial safety run. Participants will be recruited from renal departments at National Health Service tertiary hospital sites in the UK. The purpose of the safety run is to assess the tolerance of each of the three proposed Mirococept doses (60, 120 or 180 mg), before the RCT begins. Three patients will be assigned to each treatment dose, starting from the lower dose. The safety run will be considered successful if at least one dose can be taken forward to the RCT for comparison to placebo.

If safety is met, 144 participants (36 per arm excluding drop-outs) will be randomised to all doses meeting the safety criteria or placebo on a 1:1:1:1 basis. The primary endpoint is DGF, defined as the requirement for dialysis during the first week after transplantation. Safety evaluation will include the monitoring of laboratory data and the recording of all adverse events. Immunosuppression therapy, antibiotic and antiviral prophylaxis will be administered as per local centre protocols. Enrolment in the RCT is anticipated to take approximately 12 months, and patients will be followed-up for 12 months.

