### Secondary objectives

To evaluate the efficacy of Mirococept to improve the rate of recovery in grafts with DGF or IGF independent of dialysis.To determine if treatment influences renal function at 12 months (a surrogate of long-term graft outcome) and incidence of acute rejection episodes during this time.To estimate more accurately the effect size, currently estimated conservatively at 20%. This will also allow correct powering of the Phase III pivotal study.

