### Analysis

Analysis will occur at the end of the trial comparing differences in DGF proportions between each dose and the control along with CIs. Safety assessments during the randomisation stage will include routine renal function and urine tests, with further investigation (eg, renal ultrasound and Doppler) as appropriate and complement activity and Mirococept levels as per the current protocol.

In the event that DGF rate and safety outcomes are similar in more than one dosing group, the final decision on which dose to take forward to the pivotal Phase III clinical trial will include the secondary outcome measures. Of these, the most important are: functional DGF rate (where the fall in creatinine is less than 10% per day for three consecutive days); and AUC based on the drop in serum creatinine level in the first 2 weeks after transplantation where the patient does not require postoperative dialysis. If the combined primary and secondary endpoints of efficacy and the safety outcomes do not discriminate between two doses, then the lower of the two doses would be taken forward to the next trial.

This would be a confirmatory Phase III trial (to be separately funded) with two arms—the best-selected dose from the current trial vs the placebo control—each of which requiring 124 patients. Differences in DGF rates would be compared between the treatment and control arms using logistic regression adjusting for stratification factors.

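### The stated precision of ±21.1 points uses the 40 recruited per arm, not the 36 left after drop-out, and the raw estimate for a selected dose is too optimistic to re-size Phase III on its own

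*Protocol article*

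**What the plan says.** All references are to the protocol article.

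- **Size needed.** Sample size: "A sample size of 144 (36 in each arm) will be required to correctly identify the best dose of Mirococept with 90% probability". The abstract's Methods and analysis paragraph makes clear that this is a net figure: "144 participants (36 per arm excluding drop-outs) will be randomised". The reduced designs are 30 per arm with two doses and 20 per arm with one.
- **Size recruited.** Sample size: "Allowing for a 10% drop-out rate, the target sample size for a 4-arm study will be 160 participants (40 in each arm".
- **Precision.** The same section closes with "A sample size of 40 per arm will produce a two-sided 95% CI for the difference in population proportions". The half-width attached to that statement is ±21.1 points, for DGF of 30% on treatment against 50% on placebo. No figure is given at 36, 30 or 20 per arm.
- **Use of the estimate.** Secondary objectives includes estimating the effect size, now put at 20 points, and adds: "This will also allow correct powering of the Phase III pivotal study". The background subsection EMPIRIKAL-2 says much the same.
- **Estimator.** Analysis describes "comparing differences in DGF proportions between each dose and the control along with CIs". It then explains how one dose is carried forward. If DGF and safety are similar in more than one group, secondary outcomes (chiefly functional DGF and creatinine AUC) enter the decision. If these do not separate two doses, the lower one goes forward. What counts as similar is not quantified.
- **Phase III.** Analysis already gives a two-arm trial with 124 patients per arm.

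**The concern.** There are two separate issues, both about how well this trial can inform the next one.

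First, a precision statement is a planning promise and should use the number the plan expects to analyse. This plan is sized on 36 per arm after losses, but its margin is quoted at the number before losses. The reduced designs, where the interval is appreciably wider, have no margin at all.

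Second, a dose picked partly because its observed DGF rate was low will, on average, have an observed rate below its true rate. Its raw difference from placebo therefore overstates its effect. The article offers the trial's estimate as a basis for powering Phase III, and the analysis it describes does not remove this bias. If Phase III were re-sized on the raw figure, it would tend to be too small.

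**Working it through.** **1. The stated margin.** Inputs from Sample size: rates 0.30 and 0.50, two-sided 95%, n per arm. The Wald half-width is 1.96 × √[(0.30×0.70 + 0.50×0.50)/n] = 1.96 × √(0.46/n).

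- n = 40: 21.0 points. The stated ±21.1 is reproduced to within 0.1; solving for n at 21.1 gives 39.7, so 40 was used.
- n = 36: 22.2 points.
- n = 30: 24.3 points.
- n = 20: 29.7 points.

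The step from 36 to 40 is the drop-out allowance: 36/0.90 = 40. At 36 the margin is 22.2 − 21.1 = 1.1 points wider than stated. Other interval methods at 36 give 21.2 (Newcombe) to 22.6 (pooled variance). Every one of these half-widths exceeds the 20-point target effect.

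**2. Bias from selection.** Simulation with 1,000,000 runs per case, 36 per arm and placebo DGF 50%. The dose rates are assumptions, because the article gives no dose-response. Bias is the selected dose's observed difference minus its own true difference. With the lowest observed DGF always taken and ties split at random:

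- true rates 30/30/30%: +6.4 points (mean estimate 26.4 against a true 20)
- 30/35/40%: +5.5
- 30/40/40%: +4.9
- 30/50/50%, the configuration behind the sample size: +1.8
- two doses at 30 per arm: +4.7 (30/30%) or +1.4 (30/50%)
- one dose: 0

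**3. Allowing for the lower-dose tie-break.** Here the lowest dose within a margin of the best observed rate is taken. The margins are assumptions.

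- 30/30/30%: +6.0, +5.2 and +4.2 points at margins of 3, 5.6 and 10 points; +2.3 at 15 points.
- 40/30/40% (middle dose best): +4.8 to +4.9 at margins of 3 to 10 points.
- 50/30/50% (middle dose best): rises from +1.8 to +3.0 at 10 points.

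If the lowest dose is itself the best, the tie-break works the other way and the bias falls below the step 2 values. The secondary-outcome and safety steps are not modelled.

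**4. Consequence if Phase III were re-sized on the raw estimate.** n per arm = [1.96√(2p̄(1−p̄)) + 1.2816√(p₁(1−p₁)+p₂(1−p₂))]²/(p₁−p₂)², for 90% power.

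- 50% v 30%: (1.96×0.6928 + 1.2816×0.6782)²/0.04 = 124. This matches the Phase III size in Analysis.
- Raw estimate 22 points: 102 per arm; power about 84% if the truth is 20 points.
- Raw estimate 24 points: 84 per arm; power 76%.
- Raw estimate 26.4 points: 69 per arm; power 67%.

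**The case against.** The case against has real substance.

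- **The precision sentence is not false.** It names its own n, and the arithmetic at 40 is right. A reader might infer a calculation error; the text does not support that. Nor is 36 certain to be the number analysed. DGF is read at seven completed days, and Withdrawal of participants says that withdrawals are replaced and earlier data kept. The number with known DGF could lie between 36 and 40, and 1 point changes no design decision. What remains is that 36 is the plan's own net figure and the more cautious one to quote.
- **Selection is not simply the lowest observed DGF.** A reader might take the 6.4-point figure for equal doses as the expected bias. The article does not support that: safety, secondary outcomes and the lower-dose rule all enter, and they matter most when doses look alike. The tie-break check shows that the bias shrinks there but does not vanish.
- **A correction may be planned elsewhere.** The full protocol and SAP are not shown, so it cannot be said that none exists. The point rests on what the article asserts about powering, set against the one estimator it describes.
- **The 124 is sound.** A reader might infer that the planned Phase III is already undersized. It is not: 124 comes from the 50% v 30% planning rates.

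**Conclusion.** Both parts hold, at modest size.

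The planning precision is better stated as about ±22.2 points at 36 per arm. The change is about 1 point, and smaller if day-7 DGF is known for more than 36. The reduced designs would have ±24.3 and ±29.7 points.

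The raw difference for a selected dose is biased upward. With three doses at 36 per arm, the bias is roughly 2 to 3 points if only one dose works and 4 to 6.5 points if doses are similar or graded. These ranges assume 50% placebo DGF, the dose-responses above and tie-break margins of up to 10 points. A wider margin, or a lowest dose that is also the best, gives less, and a single dose going forward gives none. The harm is conditional: it arises only if Phase III is re-sized on the raw estimate. Severity is optional to minor.

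**What to change.** - In Sample size, give the precision at the number expected to be analysed: about ±22.2 points at 36 per arm, with ±24.3 at 30 and ±29.7 at 20 for the reduced designs.
- For the selected dose, report a selection-adjusted estimate and interval beside the raw one, for example by shrinkage across doses or bootstrap bias correction. A bootstrap has to replay the selection rule, so the rule must be written in a form that can be replayed.
- State that Phase III will not be re-sized on the raw estimate alone.

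The cost is one revised sentence, one extra analysis and a slightly less favourable stated margin. Recruitment and trial conduct do not change.
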